##### Objective measures of PA

Objective measurement of PA can be measured by accelerometers, pedometers, or other wearable devices [32, 33]. This approach aims to address the limitations associated with subjective self-report measures, including recall bias, social desirability bias, and inaccuracies in estimating activity intensity and duration. By utilising the objective measurement methods, a more accurate and reliable quantification of PA can be achieved, providing an accurate assessment of participants’ actual changes in PA levels before and after the intervention.

Ideally, accelerometers would be used to ensure accurate and comprehensive objective PA data, including PA duration and intensity. However, due to limited resources in this project, a pedometer (Realalt 3DTriSport 3D Pedometer; 3DTriSport Pedometer for Walking with Clip and Lanyard – Realalt) will be used to monitor participants’ PA level (i.e. step counts). The pedometer was chosen for its accuracy and affordability, and it has been previously used to measure preoperative PA levels in patients undergoing anatomical lung resection [34]. In addition, the Realalt 3DTriSport 3D Pedometer has 30 days memory, which offers an advantage by reducing the participant’s burden of daily step logging and minimising self-reporting errors. Following each of the three measurement points (T1, T2, T3), participants’ PA will be monitored continuously for 7 consecutive days using the pedometers.

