For older Chinese adults who participate in the studyAre participants willing to remain in the study for its entire duration?Are they willing to engage in PA promotion strategies, including attending workshops, using the logbook, wearing the pedometer and joining the social media group?What are their perceptions of the PA promotion strategies?

Data collection and analysisAre they willing to participate in assessments and complete the data collection at the three time points?Are the outcome measures appropriate and acceptable for older Chinese adults in the UK?

Effectiveness questionsHow do older Chinese adults’ subjective and objective PA, physical function, and quality of life change after the intervention in both the intervention and control groups?

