	**Capability**				

#### The booklet

The detailed content of the booklet is presented in Table 2. The developed booklet will include three parts: a culturally appropriate core booklet, the Chinese version of the Otago home exercise booklet, and a PA logbook. The information in the booklets was from reliable resources, including the UK Chief Medical Officers’ PA Guidelines [18], and the WHO PA guidelines [19]. The booklet also incorporates Chinese cultural factors. For example, it explains the importance of PA from the perspective of traditional Chinese medicine and philosophy and provides resources for traditional Chinese exercise programmes. A Chinese version exercise instruction booklet was translated based on the Otago home exercise booklet produced by Later Life Training [20]. Participants are also provided with a logbook to plan their PA, record daily PA, and track their achievements. All booklets are available in user-preferred languages, including Traditional and Simplified Chinese.

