### Control group (WHO leaflet group)

In the control group, participants will receive the printed leaflet of recommendations from the WHO on PA for older adults [19]. Participants will be encouraged to follow these guidelines, 150–300 min of moderate or 75–150 min of vigorous aerobic activity per week, along with balance and strength exercises twice weekly, at a time and place convenient to them. No additional support will be provided. Participants in the control group will also be provided with pedometers to collect their steps at the three time points.

The study will span 18 weeks, comprising a 12-week intervention phase and a 6-week follow-up phase. During the intervention phase, participants in the intervention group will attend workshops and receive motivational and reminder messages via a social media group. In the follow-up phase, they will be encouraged to continue their PA behaviour independently without further workshops or messages. Participants in the control group will be encouraged to follow the WHO PA guidelines during the 18-week study period and, after the study concludes, will receive the culturally appropriate PA booklet and be invited to attend one workshop.

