##### Adherence

Adherence to the PA protocol will be determined based on the type of intervention [26]. In this study, adherence will be mainly assessed by the number of workshops attended by the participants.

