##### PA behaviour outcomes (T1, T2, and T3)

PA level will be measured three times, at the baseline, after the intervention and after the follow-up. PA, being a multi-dimensional construct, presents challenges when attempting to measure all its facets using a single method. As recommended by Sylvia et al. in 2014, this study will employ a combination of objective and subjective methods to assess participants’ PA levels before and after the intervention [28]. Considering the potential discrepancies, we will prioritise the objective pedometer scores. However, qualitative interviews will be conducted to explore and explain the underlying causes of discrepancies.

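### The prioritised step-count outcome comes with no described record of pedometer wear, so part-day non-wear may pass for low activity and willingness to wear the device has no stated quantitative measure

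*Protocol article*

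**What the plan says.** Under Objective measures of PA, the article says accelerometers would be ideal, but limited resources led to a clip or lanyard pedometer whose output is described only as step counts. After each of baseline, 12 weeks and 18 weeks, activity is "monitored continuously for 7 consecutive days using the pedometers". The 30-day memory is given as an advantage that reduces the participant's "burden of daily step logging and minimising self-reporting errors".

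Under PA behaviour outcomes, the article sets the order of precedence between pedometer and questionnaire: "Considering the potential discrepancies, we will prioritise the objective pedometer scores".

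The device has different roles in the two arms. Under Social media group, it is both an intervention component for monitoring and goal setting and a data collection tool. Under Control group, it is for measurement only: "Participants in the control group will also be provided with pedometers to collect their steps at the three time points". The logbook is part of the intervention booklets: "Participants are also provided with a logbook to plan their PA, record daily PA, and track their achievements".

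The research questions in the Introduction ask whether participants are willing to take up the strategies, including "using the logbook, wearing the pedometer and joining the social media group".

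**The concern.** A step total does not show how long the device was worn. A day on which it was put on at noon and a quiet day with full wear can give the same number. Eligibility makes this harder to sort out afterwards: participants must fall short of the PA guidelines and need only be able to walk around at home independently, so truly low days are expected. A low-step cut-off would remove real inactivity along with non-wear.

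Two things are at stake.

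- **The outcome summaries.** Data analysis plans means and SDs by group and 95% confidence intervals for change. Incomplete wear lowers mean steps. If wear differs between time points, the change estimate is also wrong: too low if wear falls off after baseline, too high if it improves.
- **The feasibility question on wear.** A feasibility trial is the place to learn whether this population will wear the device. Table 2 already reports an interviewee saying that people like them had been given fitness trackers and disliked using them. The reasons given, a small screen and frequent charging, may not all apply to this device.

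An analysis plan can set a rule for valid days, but it cannot recover wear information that was not collected.

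**Working it through.** The article gives no figure for wear or for expected steps, so there is no stated number to reproduce on this point. The check has two parts.

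**1. Where could wear be recorded?**

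| Source in the article | What it captures | Does it record wear? |
|---|---|---|
| Objective measures of PA | Step counts in device memory, 7 days per time point | Not described |
| Logbook (The booklet) | Plans, daily PA and achievements, intervention arm only | Not mentioned |
| Adherence | "adherence will be mainly assessed by the number of workshops attended by the participants" | No |
| Intervention fidelity | Whether the pedometer was received | No, receipt only |
| Table 4, adherence | Workshop attendance | No |
| Table 4, data completeness | Go at 90% or more; a valid pedometer day is not defined | No |
| Qualitative interviews | Experience of the intervention and measures, at the end of the study | In part: about 50% invited, mostly intervention arm, few controls |

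No source described in the article gives a wear measure for all participants in both arms.

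**2. How large could the effect be?**

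From the document: a window of 7 days. Assumed, because the document gives neither: the number of affected days and the true mean S in steps/day.

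*Whole unworn days.* If k of 7 days are unworn and averaged in as zero, the recorded mean is S × (7 − k)/7, a relative loss of k/7:

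- k = 1: 1/7 = 14.3%
- k = 2: 2/7 = 28.6%
- k = 3: 3/7 = 42.9%

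*Part-day non-wear.* If a fraction f of the day's steps is missed on each of k days, the loss is k × f/7. With f = 0.5:

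- k = 2: 2 × 0.5/7 = 14.3%, the same as one wholly unworn day, with no zero in the record
- k = 4: 4 × 0.5/7 = 28.6%

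*Unequal wear between arms.* If one arm has one more wholly unworn day than the other and activity is the same, the false difference in recorded means is S/7:

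- S = 3,000: 3,000/7 = 429 steps/day
- S = 5,000: 5,000/7 = 714 steps/day
- S = 7,000: 7,000/7 = 1,000 steps/day

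Two extra days double these, to 857, 1,429 and 2,000.

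*What a wear record repairs.* Averaging only over days recorded as worn gives (7 − k) × S/(7 − k) = S. The bias goes if activity does not differ between worn and unworn days. The same holds for part-worn days if the card identifies them.

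**The case against.** The strongest case against this point has five parts.

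- **The article is a condensed document.** The case report form, supplementary files and any analysis plan are not shown, and the assessment schedule (Table 3) is a missing figure. Valid-day rules commonly sit in such documents. This stands: the point can say only that the article describes no wear record, not that none exists. The lack of a valid-day rule would not be a finding by itself. What remains is the stated choice to use stored step counts in place of daily logging, with no described source of wear information.
- **Avoiding step logging is not the same as refusing to record wear.** This is fair. The article's rationale concerns writing down counts and leaves room for a simple wear tick.
- **Unworn days are not said to count as inactive.** A reader might infer that they do, or that stored zeros count as complete data. No section says so. Data are to be checked for completeness and accuracy, and missing data reported. A near-zero day in someone who can walk at home would probably be noticed and could be set to missing. This answers the whole-day case but not the part-day case.
- **The trial can still say something about willingness to wear.** A reader might infer that its question cannot be answered. That is too strong: interviews cover the intervention and the measures, and stored daily steps give a rough proxy. What is lacking is a stated quantitative indicator.
- **No decision rests on a difference between arms.** A reader might infer a false treatment effect. Data analysis rules out formal hypothesis tests and between-group comparisons, and step count enters no progression criterion except possibly data completeness. Less wear among controls is plausible from the device's two roles, but nothing in the article shows it. Baseline is taken before randomisation, and interviews will explore disagreements between pedometer and questionnaire. These limits stand, though group means and changes will still be reported.

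**Conclusion.** The point holds in a limited form. The prioritised objective outcome is a step count read from device memory, and the article describes no record of wear in either arm. Part-day non-wear therefore cannot be told from low activity, and no later analysis rule can recover the distinction. The question on willingness to wear the pedometer has no stated quantitative measure.

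The size is illustrative. A loss of 14% per wholly unworn day assumes that the day is averaged in as zero, which the article does not state. The part-day figures assume that half the day's steps are missed. The differences of 429 to 1,000 steps/day assume true means of 3,000 to 7,000 and one extra unworn day in one arm. They show what incomplete wear could do to the reported means; they do not predict that it will happen.

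**What to change.** 1. In both arms, add a card with one tick per day for each 7-day step window (worn all day, part of the day, not worn), returned when the device is read.
2. Define the outcome as mean steps per valid worn day. State in advance which ticks make a day valid and how many valid days are needed; otherwise the step outcome for that time point is missing.
3. Report valid-wear days by arm and time point as a feasibility outcome, and count them within data completeness.

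The cost is three cards and 3 × 7 = 21 ticks per participant, or up to 30 × 3 = 90 cards at the planned 30 participants. The downsides are a few seconds of self-report per day, which brings back a little of the burden the device was chosen to reduce, and some step weeks reclassified as missing. On and off times are not needed.

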#### Secondary outcomes

The following secondary outcomes will be measured at three time points: T1, T2, and T3.

##### COM-B questionnaires

Based on the COM-B framework, the PA promotion strategies in this study aim to improve older Chinese adults’ capability, motivation, and opportunity for PA, making it essential to assess changes in these perceptions before and after the intervention.

Brief COM-B questionnaires will be used to assess the perceived capability, opportunity, and motivation for PA behaviour among older Chinese adults in the UK. The acceptability, reliability, and validity of this brief measurement tool have been tested by Keyworth [35]. The questionnaires have been adapted to understand behaviour, such as hand hygiene behaviour among hospital staff [36], and PA among adults in the UK during the COVID-19 pandemic [37]. The questions have been adapted based on the findings of the interview with the target population. Example questions relate to opportunities like “There are suitable places and programs near me for PA, such as parks, swimming pools, or opportunities for dancing and Tai Chi”. The social environment is supportive of PA, such as exercise groups, encouragement from family and friends, and sufficient time to be active. Participants responded on a scale of 0 (strongly disagree) to 10 (strongly agree). Both total and domain-specific analyses of the COM-B questionnaire will be conducted to assess overall and domain-level changes in capability (physical and psychological), opportunity (physical and social), and motivation (reflective and automatic) for engaging in PA.

##### Physical function

The Short Physical Performance Battery (SPPB) will be used to assess the potential change of physical function before and after the PA promotion strategies [38]. This is an objective tool used to measure balance, lower extremity strength, and functional capacity in older adults aged 65 and above [39]. The test assesses functional mobility across three domains: walking, sit-to-stand, and balance. Additionally, the SPPB is a brief assessment, designed to minimise participant burden.

##### Quality of life

The CASP-12 (Control, Autonomy, Self-realisation, and Pleasure-12) questionnaire will be used to measure older adults’ health-related quality of life [40]. This questionnaire consists of 12 items, each rated on a scale from 1 (often) to 4 (never). The items are summed to calculate a total score. CASP-12 has recently been tested among older Chinese migrants in New Zealand, which shows evidence for the validity and reliability of the CASP-12 as a QOL measure to be used with older Chinese migrants [41].

##### Adverse events

A safety reporting protocol will be followed for managing related and unexpected serious adverse events (SAEs) and directly attributable adverse events (AEs). All AEs will be documented in the Case Report Form (CRF). Participants will be asked to inform the researcher of any injuries after seeking appropriate medical assistance. They could stop the exercise at any time if they experienced any adverse. If a serious adverse event (AE) occurs, it will be reported to the research team to assess whether further reporting to the trial sponsor and ethics committee is required, in line with the safety reporting protocol.

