#### Eligibility criteria for participants

We will recruit participants who meet the following inclusion criteria:Adults aged 60 years or above;Self-identified as Chinese ethnicity;Speaking either Cantonese, Mandarin, and/or English;Able to read and write Chinese or English;No time requirement for their stay in the UK, but they should have settled in the UK as residents and not as tourists.Self-report not meeting the PA guidelines for older adults (engaging in less than 150 min of moderate-level PA each week and performing balance, strength, and flexibility exercises less than twice a week);Self-report being able to walk around at home independently;Can provide informed consent.

We however will exclude:Those who self-report that they already meet the PA guidelines (engaging in more than 150 min of moderate-level PA each week and performing balance, strength, and flexibility exercises more than twice a week), as this study focuses on older Chinese adults with insufficient PA.Those who plan to be away from Manchester for more than 2 months during the intervention period.Participants with diseases where exercise is contraindicated will be excluded to ensure the safety of the participants (see Table 1). A self-reported approach will be used to identify these conditions, including cognitive impairment, as it is considered more acceptable by PCIE participants than formal assessments such as the MMSE (Mini-Mental State Examination), which were viewed as burdensome. To mitigate potential bias, the research team will monitor participants throughout the study. Participants who show signs of impairment after giving consent, such as difficulty completing data collection or following instructions, will be excluded.

**Table 1 Tab1:** List of conditions contraindicating exercise participation

Participants who self-report any of the following diseases will be excluded:
o Uncontrolled pain;
o Uncontrolled angina;
o Major heart surgery in the last 6 months
o Resting SBP > 180 mmHg or resting DBP > 100 mmHg
o Tachycardia > 100 bpm
o Acute systemic illness (cancer, pneumonia)
o Visual or vestibular disturbances
o Significant drop in BP during exercise
o Unstable or acute heart failure
o Unable to maintain seated upright posture due to neurological deficits
o Recent injurious fall without a medical examination
o Serious impaired cognition (to the extent of being unable to follow simple movement instructions)

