##### Retention rate

Randomised participants may exit the trial for various reasons. A research journal and case report form will be created to record the number of participants who (1) complete all the follow-up data collection; (2) fully withdraw, where participants refuse to engage in any future activities (including intervention and assessment); (3) loss to follow-up, which should only be considered after the 12-week and/or 18-week visits are due and all contact attempts have been exhausted, but still cannot complete the data collection; and (4) death or other serious adverse events. It is recommended not to automatically treat all withdrawals as a complete exit from the trial [25]. Participants should not be fully withdrawn for discontinuing or noncompliance with the intervention. For example, participants may choose to withdraw from attending the workshop or participating in the social media group, but may still be willing to engage in data collection activities. Alternatively, their participation may need to be discontinued based on clinical judgement. We will make every effort to collect as much data as possible to maintain the integrity of the study. The reasons for participants’ exit from the trial will be carefully recorded separately.

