### Intervention fidelity

Fidelity refers to how closely the delivered intervention matches the originally planned or designed protocol [44]. In this study, intervention fidelity reflects the extent to which the three main components of the intervention are delivered as planned. A fidelity checklist will be used to systematically assess these components and will be completed by the lead researcher. The checklist can be found in Appendix 2. Specifically, fidelity is assessed by checking:

Whether all participants in the intervention group receive the culturally tailored PA promotion booklets; Whether the three-monthly workshops are organised and delivered according to the planned time and content; Whether at least three motivational messages are sent to participants via the social media support group as intended each week. Additionally, fidelity monitoring includes recording whether all participants receive a pedometer and resistance band to support home-based exercise.

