### Progression criteria

Progression criteria for a full RCT are developed following the guidance of Avery et al. [45]. The thresholds are informed by findings from earlier reflective research [46, 47], internal team discussions, and consultation with the PCIE group. In line with Mellor et al. (2023), we define progression criteria across multiple trial domains, including recruitment, retention, data completeness, fidelity, safety, and intervention acceptability, drawing on both qualitative and quantitative data [48]. Full details of the progression criteria are provided in Table 4.

**Table 4 Tab4:** Progression criteria

Domain	Go-proceed with RCT	Amend-proceed with change	Stop-do not proceed
Recruitment	If at least 30 participants are recruited within eight weeks	If at least 16–29 participants are recruited within eight weeks	If ≤ 15 participants are recruited within eight weeks
Retention	If ≥ 24 participants (80%) complete the 18-week follow-up	If 20–23 participants (64–79%) complete the 18-week follow-up	If ≤ 19 participants (63%) complete the 18-week follow-up
Adherence	If an average of ≥ 12 of the 15 participants (80%) attend each workshop	If an average of 8–11 of the 15 participants (53–73%) attend each workshop	If an average of ≤ 7 of the 15 participants (46%) attend each workshop
Data completeness	If ≥ 90% of the data is completed	If 70–89% of the data is completed	If ≤ 69% of the data is completed
Fidelity	If all core intervention components are delivered as planned	If minor deviations in the delivery of core components	If major deviations in the delivery of core components
Safety	No serious adverse events; minor events, if any, are manageable and anticipated	Some minor adverse events; no serious harm, but may need adjustments	Serious adverse event(s) related to the intervention were reported
Acceptability	Qualitative data indicate strong acceptability of the intervention components	Qualitative data indicate general acceptability, with changes needed	Qualitative data indicate the intervention was unacceptable

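### The only described route for an adverse event to reach the researcher is participant-initiated injury reporting, which risks missing minor events that inform the Safety progression row

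*Protocol article*

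**What the plan says.** All references are to the Protocol article.

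- **How an event becomes known.** Adverse events: "Participants will be asked to inform the researcher of any injuries after seeking appropriate medical assistance".
- **How a known event is recorded.** Same section: "All AEs will be documented in the Case Report Form (CRF". The section also refers to a separate document: "A safety reporting protocol will be followed for managing related and unexpected serious adverse events (SAEs) and directly attributable adverse events (AEs". That document is not shown.
- **Serious events.** Retention rate lists what the research journal and case report form will count for randomised participants, including "4) death or other serious adverse events".
- **Contact in the intervention arm.** The Workshop section schedules three sessions of about 90 minutes over 12 weeks. The Social media group section adds a WeChat or WhatsApp group. Intervention fidelity checks "Whether at least three motivational messages are sent to participants via the social media support group as intended each week".
- **Contact in the control arm.** Control group: "No additional support will be provided". Both arms are assessed at 12 weeks (T2) and 18 weeks (T3).
- **Use of the data.** Safety is one of the seven domains in Table 4. Its Amend cell reads "Some minor adverse events; no serious harm, but may need adjustments". Its Go cell also allows minor events, provided that they are manageable and anticipated. Its Stop cell concerns reported serious events related to the intervention.

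**The concern.** Recording an event and finding it are separate steps. The article promises that every event will be documented, but the only finding step it describes depends on the participant coming forward, and it mentions injuries alone. A fall without injury, muscle soreness, dizziness or a flare of an existing condition is not clearly covered. If the phrase about medical help is taken as a condition, an injury managed at home is not covered either.

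The participants are insufficiently active adults aged 60 or over, screened for contraindications by self-report. The intervention arm does strength and balance exercises at home with a resistance band, and the control arm is encouraged to reach the WHO activity levels. Minor events are therefore plausible in both arms, and they are the kind least likely to be volunteered. In the Safety row a missed event can only make the trial look safer, so the error tilts from Amend towards Go.

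A second, smaller issue is that volunteering depends on opportunity. During the 12-week intervention phase one arm meets the researcher and shares a chat group, and the other does not. Simple counts by arm could then reflect contact as well as harm.

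**Working it through.** **1. Is another finding route described?** Setting the relevant sections side by side:

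| Section | What it provides | Does it elicit minor events in both arms? |
|---|---|---|
| Adverse events | Participant reports injuries; all events entered on the form; safety reporting protocol cited | No question or time point described |
| Retention rate | Deaths and other serious events, reasons for exit | Serious events and exits only |
| Eligibility criteria | "the research team will monitor participants throughout the study" | No; the stated purpose is to detect impairment that would lead to exclusion |
| Sociodemographic | 6-month fall history at baseline; GP details for reporting | No matching follow-up item described |
| Qualitative interviews | About 50% invited at the end, mostly intervention arm | Topics are trial processes, the intervention and measurements |

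**2. Contact after randomisation.**

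- Intervention: 2 assessments, 3 workshops and at least 3 × 12 = 36 group messages.
- Control: 2 assessments. Nothing else is described between the baseline measurement period and T2.

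The messages are motivational and are not enquiries about harm. They show how much opportunity there is to mention an event, not how many times anyone is asked.

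**3. Size.** The article states no figure for event risk or reporting, so there is none of its own to reproduce on this point. The arm size follows from its sample-size section: 24 / (1 − 0.20) = 30, or 15 per arm, which matches the 15 used in the Adherence row of Table 4.

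For the Safety row, take the 15 intervention participants. Let r be the true risk that a participant has a minor event and c the probability that it becomes known. Both are assumed, and participants are taken as independent. The chance that no affected participant is recorded is (1 − r × c)^15:

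| True risk r | c = 1.0 | c = 0.8 | c = 0.5 | c = 0.3 |
|---|---|---|---|---|
| 10% | 21% | 29% | 46% | 63% |
| 20% | 4% | 7% | 21% | 40% |
| 30% | 0.5% | 2% | 9% | 24% |

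For example, r = 10% and c = 0.3 gives 0.97^15 = 0.63, and full capture gives 0.90^15 = 0.21. With good capture (0.8) the loss is small. With poor capture it is large.

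**4. Between arms.** With r = 20% in both arms, expected affected participants recorded are 15 × 0.20 × c. Capture of 0.8 against 0.5 gives 2.4 against 1.5, and 0.8 against 0.3 gives 2.4 against 0.9, where the truth is 3.0 in each arm. The ratio of the two counts is simply the assumed ratio of capture, so these figures illustrate a mechanism and are not evidence of its size.

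**The case against.** The strongest reply is that this is a condensed article. How events are elicited commonly sits in a safety reporting protocol and a case report form, the first is cited, and the schedule in Table 3 is not legible here. Adverse events also stand under Secondary outcomes, which are said to be measured at T1, T2 and T3. The phrase about medical help can be read as an order of actions (get care, then tell us) and not as a filter.

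Much of this stands. A reader might infer that adverse events are captured solely through volunteered injuries. The documents do not support that: serious events have a second route under Retention rate, and the safety reporting protocol may require active questioning. A reader might also infer that counts will be too low and will differ between arms. That is a risk, not an established fact, because no rate is given.

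A further inference would be that the package could be judged more harmful than the leaflet. The Data analysis section plans no between-group comparison, and no cell of the Safety row compares arms. The arm that matters most for that row is also the one with more contact. Finally, Go and Amend differ on whether adjustment may be needed, not on a count of minor events.

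The reply does not remove the point, because the article is not silent. It states a finding route, and that route suits the Safety row poorly. If the general T1 to T3 statement is meant to cover adverse events, the Adverse events section should say so. If the medical-help phrase means sequence, it should be worded that way. The limit to injuries remains on either reading.

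**Conclusion.** The point holds in limited form. The one described route for an adverse event to reach the researcher is participant-initiated and confined to injuries, apart from serious events counted under Retention rate. Followed as written, it risks missing minor or non-injury events that inform Go versus Amend, and the direction of error is towards Go. Because contact differs by arm during the 12-week intervention phase, descriptive counts by arm should not be read as comparable. That affects interpretation only, since no formal comparison is planned.

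The size cannot be derived from the article. On assumed true risks of 10% to 30% and capture of 30% to 80%, the chance of recording no affected participant among 15 ranges from 2% to 63%, against 0.5% to 21% with full capture. The conclusion assumes that the safety reporting protocol does not already require the same questions of both arms. If it does, only a sentence in the article is needed. The change is worth making because it is cheap and a progression domain rests on these data.

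**What to change.** 1. At the existing T2 and T3 visits, ask every participant in both arms the same scripted question on falls, injuries, new symptoms and hospital contact since the last visit, whether or not medical help was sought. Reuse the baseline fall-history item with its recall period adapted to the interval.
2. List spontaneous reports separately from solicited ones in any summary.
3. Let the Safety row draw on all recorded events, marking which were solicited, and never leave out a serious event because it was reported spontaneously.
4. Reword the reporting sentence in the Adverse events section so that it is clear whether seeking care is a condition for reporting or only comes first, and so that it is not limited to injuries.
5. If the safety reporting protocol already requires the questioning in step 1, say so in that section.

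The cost is a few minutes at two visits that take place anyway and one page on the case report form. The downside is that more minor events will be recorded, so the team should expect higher counts than volunteered reporting would give.
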